### Withdraw criteria

2.9

Patients with any of the following conditions will be withdrawn from this study: being found having any of the exclusive criteria after enrollment; takes glucosteroids or other immunosuppressants during the study; has intolerable side effects of drugs; has any serious adverse event that makes subjects unsuitable for continuation, such as severe infection, uncontrollable hyperglycemia, and/or hypertension; the patient asks to withdraw; other situations which the researchers believe makes the patient not appropriate to continue.

### Sample size

2.10

In a preliminary screening from January 2010 to December 2017 in our center's Renal Treatment System, a total of 87 IMN patients were identified. The average amount of proteinuria in this population was 2.89 ± 0.62 g/d at the time of diagnosis. According to the clinical data of our center, combined with the published data on proteinuria in IMN patients, we expect that the experimental treatment is superior to the control when mean decrease in proteinuria in the intervention group is 2.0 g/d higher than that in the control group. Therefore, the sample size calculated with type I error of 0.05 (bilateral) and a randomization ratio of 1:1 to provide a power of 80% to detect an effect size of 2 g/d is 9 per group. The total number increased to 20 considering a loss of follow-up rate of 10%. Minimum loss to follow-up is expected given such small sample size and intensive clinic visits during follow-up. Therefore, 20 subjects will be included in this study.

### Data analysis

2.11

Continuous data will be described by mean ± standard deviation or median (interquartile range). Classified data will be described by the number and percentages. Chi-square test or Fisher exact test (if expected number in 1 cell is below 5) for categorical variables and Student *t* test or Wilcoxon rank sum test for continuous variables will be applied to detect the differences between the intervention and the control groups. Due to the potential spontaneous remission in IMN patients, analysis of covariance will be conducted using proteinuria at baseline as a covariant to further evaluate the difference between these 2 groups. A 2-tailed *P* < .05 will be considered to be significant. Statistical analysis will be performed using SPSS version 24.0 (IBM Corporation, Armonk, NY) and RStudio for Windows, version 4.0.3 (RStudio, Inc., Boston, MA, USA) and supervised by a skilled statistician (QL).

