## Abstract

**Objective::**

Tripterygium wilfordii multiglycosides has been demonstrated to be effective in reducing proteinuria and alleviate edema in patients with chronic kidney disease. We aim to evaluate its efficacy and safety in idiopathic membranous nephropathy.

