**Methods and analysis::**

This is an randomized, open-labeled, controlled clinical trial. Twenty eligible patients with idiopathic membranous nephropathy will be randomly assigned into the intervention group and the control group at a rate of 1:1. Patients in the intervention group will receive tripterygium wilfordii multiglycosides tablets (1–1.5 mg/kg body weight/d, orally) in addition to the original treatment of angiotensin converting enzyme inhibitor/angiotensin receptor blocker, while the control group will continue with the original treatment of angiotensin converting enzyme inhibitor/angiotensin receptor blocker. The treatment course is 6 months, and clinical variables of patients will be measured at baseline and each monthly follow-up. The primary efficacy outcome measure is absolute decrease in urinary protein quantity after 6 months of treatment compared with baseline at randomization. The secondary efficacy outcome measures include absolute decrease in urine albumin-creatinine ratio in spot urine after 6 months of treatment compared with baseline at randomization, the percentage of patients who reached effective clinical response, and the percentage of patients who developed composite renal endpoint. Safety outcome measures include incidence of adverse events, incidence of serious adverse events, and death.

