## Introduction

1

Idiopathic membranous nephropathy (IMN) is one of the common pathological types of primary nephrotic syndrome in adults, with a peak age around 40 to 50 years old.^[1,2]^ In China, IMN accounts for 30.2% of primary glomerular disease and is the leading cause of nephrotic syndrome in adults over 40 years old.^[3]^ Immunosuppressive therapy is the current first line treatment of IMN, and its efficacy has been confirmed by a large number of high-level evidence.^[4]^ For IMN patients who have moderate to low risk for progressive renal function decline, the latest version of Kidney Disease: Improving Global Outcomes guideline of Chronic Glomerular Disease^[5]^ still recommends a “wait and see” policy in addition to treatment of angiotensin converting enzymes inhibitor (ACEi) or angiotensin receptor blockers (ARB). However, we have found a considerable number of patients with proteinuria below 3.5 g/d suffered from significant edema symptom, making the supporting treatment of full-dose ACEi/ARB alone less well accepted in this population, especially in the elderly.

Tripterygium wilfordii multiglycosides is extracted and purified from the root xylem of *Tripterygium wilfordii* Hook F (TwHF), which is a member of the Celastraceae family of perennial vine-like plants.^[6]^ It has been reported in literature and also shown by our experience that tripterygium wilfordii multiglycosides can reduce proteinuria and alleviate edema symptom of patients with chronic kidney disease,^[7–9]^ through mechanisms including but not limited to activating T cells^[10]^ and regulating nuclear factor κB pathway.^[7,10,11]^ Most experience of tripterygium wilfordii multiglycosides in IMN so far came from observational studies with limited number of subjects. There is still a lack of solid evidence to support its use in IMN patients.

This is a randomized, open-label, controlled trial to investigate the efficacy and safety of tripterygium wilfordii multiglycosides in IMN patients who would be classified as moderate to low risk according to Kidney Disease: Improving Global Outcomes guideline. The results might be used to improve our understanding of this drug in treating IMN and provide evidence for clinical practice. We hypothesized that tripterygium wilfordii multiglycosides combined with ACEi/ARB is superior to ACEi/ARB alone in treating IMN.

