#### Safety outcomes

2.7.2

Since the major adverse effects of tripterygium wilfordii multiglycosides are liver dysfunction and gonadal suppression,^[12,13]^ we will closely monitor manifestations of these 2 aspects in addition to routine practice on safety surveillance. Therefore, safety outcomes in this study will include but not limited to the following:

Clinical: blood pressure, edema, anemia, menstruation status in the women;Blood biological tests: complete blood cell count; serum creatine, albumin, alanine aminotransferase, aspartic aminotransferase, total bilirubin, direct bilirubin, indirect bilirubin, lactate dehydrogenase.

An adverse events (AE) mean any adverse event that happens during the study duration, regardless of its relevance to the experimental intervention. Any adverse event happens will be recorded in details and followed up until resolution. Serious AE includes life-threatening conditions, hospitalization, prolonged hospitalization, transient or permanent disability, and death. Any serious AE should be reported to the sponsor within 24 hours after occurrence, recorded, and followed as AE.

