## Discussion

3

IMN is one of the most common primary glomerular diseases in China, especially in the elderly, and its prevalence is rising over recent years.^[14]^ Patients who are classified as low risk of renal function decline based on Kidney Disease: Improving Global Outcomes guidelines often present with obvious lower extremities edema, which make the supportive treatment of ACEi/ARB alone less well accepted.

Tripterygium wilfordii multiglycosides has been used to treat rheumatic disease in China for many years. Evidence from a number of observational studies indicated this drug can reduce proteinuria and alleviate edema of patients with chronic kidney diseases including IMN.^[12]^ These findings are consistent with our own clinical experience. Previous studies have shown that tripterygium wilfordii multiglycosides can significantly reduce the production of inflammatory cytokines such as tumor necrosis factor α, Interleukin-1β, and monocyte chemoattractant protein-1 and ameliorated oxidative stress.^[10]^ It can attenuate inflammatory response by down-regulation of nuclear factor κB signaling pathway.^[10,11]^ In addition, tripterygium wilfordii multiglycosides can also promote the structural repair of podocyte hiatus membrane protein.^[7]^ These mechanisms might explain the reduction of proteinuria observed. However, there is still a lack of high-level evidence for using this drug to treat IMN. Therefore, we designed this randomized, open-label, controlled trial to investigate its efficacy and safety in treating this disease.

Tripterygium wilfordii multiglycosides has known side effects, of which hepatotoxicity and menstrual disorder are the top 2. Excessive dose and prolonged duration are the main reasons to cause adverse effects.^[13]^ The reported incidence of reproductive toxicity among tripterygium wilfordii multiglycosides users thus far was between 3.4% and 7.9%.^[14]^ In our study, we will strictly calculate and control the dose and treatment duration of each subject to avoid drug overdose and accumulation. Meanwhile, we will closely monitor adverse effects in monthly follow up visit, and we also add 1 follow-up (Visit 3) to monitor potential adverse effects of tripterygium wilfordii multiglycosides. If any signs intolerable side effects relevant to the experimental drug occurs, we will withdraw the subject immediately, take appropriate measures, and follow up until the side effect resolves.

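### Safety is a stated objective, but the only between-group rule in section 2.11 is a generic P < .05 test, which with 10 patients per arm will usually miss any toxicity affecting fewer than about 4 in 10 treated patients

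*Protocol article*

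**What the plan says.** The Abstract states the objective as "We aim to evaluate its efficacy and safety in idiopathic membranous nephropathy", and the Introduction describes a trial "to investigate the efficacy and safety of tripterygium wilfordii multiglycosides in IMN patients". The Abstract names the safety endpoints: "Safety outcome measures include incidence of adverse events, incidence of serious adverse events, and death". Section 2.7.2 adds clinical items, including menstruation status, and a panel of blood tests that includes liver enzymes and bilirubin, under the wording "safety outcomes in this study will include but not limited to the following".

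Section 2.11 has no separate safety paragraph. Categorical data are described by counts and percentages, and continuous data by mean and SD or by median and interquartile range. The arms are then compared by "Chi-square test or Fisher exact test (if expected number in 1 cell is below 5) for categorical variables" and by a t or Wilcoxon test for continuous variables. These tests "will be applied to detect the differences between the intervention and the control groups", and "A 2-tailed *P* < .05 will be considered to be significant". No confidence interval is mentioned.

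Section 2.10 bases the sample size on a proteinuria difference alone. The Discussion gives one toxicity range: "The reported incidence of reproductive toxicity among tripterygium wilfordii multiglycosides users thus far was between 3.4% and 7.9" per cent. It also names hepatotoxicity and menstrual disorder as the two leading side effects, without a rate for hepatotoxicity.

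**The concern.** A significance test suits a question where a difference is expected and the trial is large enough to show it. For safety with 10 patients per arm, the useful question is which rates of harm the data can exclude, and a P value does not answer it. Most outcomes that would worry a clinician, such as 3 or 4 treated patients with liver injury and no controls, would be labelled non-significant.

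The Discussion hopes that the results may support use of the drug and inform therapeutic decisions. One of the two stated objectives would then rest on a comparison that can rarely come out positive at plausible toxicity rates, and nothing in the analysis section tells the reader how little a negative result means.

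**Working it through.** **Inputs from the protocol.** 10 patients per arm (section 2.2); two-sided 0.05, with Fisher's test when an expected count is below 5 (2.11); reproductive toxicity 3.4% to 7.9% (Discussion). The protocol states no power or precision for any safety outcome, so there is no safety figure to reproduce. The arm size follows from its 9 per group: 9 / 0.9 = 10. Whether 9 follows from the stated spread of proteinuria is a separate matter and does not affect this point.

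**Assumptions.** Control event rates of 0% and 10%, and all treated rates other than 3.4% and 7.9%, are chosen to show the range.

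**Step 1: the smallest significant result.** With a events in 10 treated and none in 10 controls, the two-sided Fisher P is 2 × C(10,a) / C(20,a).
- a = 4: 2 × 210 / 4845 = 0.087, not significant.
- a = 5: 2 × 252 / 15504 = 0.033, significant.

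With one control event, 6 of 10 gives P = 0.057 and 7 of 10 gives P = 0.020. The chi-square branch applies only when the two arms have exactly 10 events in total. There 7 v 3 gives P = 0.074 and 8 v 2 gives P = 0.007, so it does not change which tables are significant.

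**Step 2: power for event rates.** With no control events, power is P(X ≥ 5) for X ~ Binomial(10, p). With other control rates it is the summed probability of all significant tables with more events on the drug.

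| True rate on drug | 10 v 10, control 0% | 10 v 10, control 10% | 9 v 9, control 0% |
|---|---|---|---|
| 3.4% | 0.001% | below 0.001% | 0.001% |
| 7.9% | 0.06% | 0.02% | 0.03% |
| 20% | 3.3% | 1.2% | 2.0% |
| 30% | 15% | 5.7% | 9.9% |
| 40% | 37% | 15% | 27% |
| 50% | 62% | 30% | 50% |
| 60% | 83% | 47% | 73% |
| 70% | 95% | 67% | 90% |

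**Step 3: continuous laboratory values.** For a two-sample t test with n per arm, the noncentrality is d × √(n/2), where d is the shift in SD units. Power reaches 80% at d of about 1.33 with 10 per arm and 1.41 with 9. A shift of 0.5 SD has power 0.185 with 10 per arm and 0.170 with 9.

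**Step 4: what a clean result would show.** The exact upper limit for 0 events in n is 1 − 0.025^(1/n) (two-sided 95%). For n = 10 it is 30.8%; the one-sided 95% limit, 1 − 0.05^(1/10), is 25.9%. If all 10 treated patients were at risk, the chance of seeing no reproductive-toxicity case at all is 0.966^10 = 70.8% at 3.4% and 0.921^10 = 43.9% at 7.9%.

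**Step 5: menstrual change.** Only women at risk count, so the denominator is likely to be below 10. With an illustrative 5 women per arm, significance needs 4/5 v 0/5 (P = 2 × 5 / 210 = 0.048). With 3 per arm, even 3/3 v 0/3 gives P = 2 × 1 / 20 = 0.10, so no result could be significant.

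**The case against.** The case against has four parts.

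- **It is an omission that the SAP may fill.** A condensed article may leave safety reporting to the full plan, and section 2.11 does not exclude intervals. This has some force for the detail of interval methods. But the article does not defer the between-group method. It states one, and that method fits safety badly.
- **Safety is not named in section 2.11.** This is correct. The rule reaches safety outcomes only because it covers all categorical and continuous variables. A reader might infer that the protocol means to treat P > .05 as proof of safety, but no sentence says so.
- **Other safety handling exists.** This also stands. Numbers and percentages are planned, so 4/10 v 0/10 would be visible as 40% v 0%. Sections 2.7.2, 2.8 and 2.9 provide for monitoring, follow-up of every adverse event, an extra visit at two weeks, and withdrawal for intolerable effects. The test is therefore not the only treatment of safety; it is the only stated rule for comparing the arms. Monitoring protects participants but does not correct an inference drawn from the comparison.
- **The limit is trial size.** This is true: detecting 7.9% against 0% with 80% power would need about 95 per arm (119 with a continuity correction). Intervals add no information about the drug. They do show how little 20 patients can exclude, which a P value hides.

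**Conclusion.** The point holds as an inexpensive improvement. The stated comparison cannot answer the safety question at the only toxicity range the protocol gives: power is under 0.1% at 3.4% to 7.9% against an assumed 0% in controls. Up to about 4 in 10 treated patients affected, a non-significant result remains the more likely one (power 37% at 40%), and a 10% control rate lowers power further.

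A reader might go on to infer that the test would come out negative almost whatever the toxicity. The figures do not support that. Against 0% in controls, power is 62% at 50%, 83% at 60% and 95% at 70%, and laboratory shifts of about 1.3 SD or more have at least 80% power.

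The size of the problem rests on the assumed control rates and on arms of exactly 10. Simple randomization (section 2.5) may give unequal arms, and the menstrual outcome has a smaller denominator. The primary efficacy analysis is not affected.

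**What to change.** In section 2.11, separate safety from the efficacy tests and replace the P < .05 comparison as follows:

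1. For adverse events, serious adverse events, liver-test abnormality and menstrual change, give the number and percentage per arm with exact (Clopper-Pearson) 95% intervals. Use the women at risk as the denominator for menstrual change.
2. Give the between-arm risk difference with an exact or score-based 95% interval, and name the method in advance.
3. For continuous safety laboratory values, give the mean between-arm difference with its 95% interval.
4. Add a sentence such as: Absence of a significant difference will not be interpreted as evidence of safety; the upper confidence limit will be reported as the highest rate that the data do not exclude. With 10 treated patients and no events, this limit is about 31%.

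The cost is a few sentences and routine calculations in the R environment that is already planned, with no added patients, visits or tests. The downside is that the report must show wide intervals and make a weaker safety statement.

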#### Efficacy outcomes

2.7.1

Primary efficacy outcome is absolute decrease in proteinuria after 6 months of treatment compared with baseline at randomization.

Secondary outcomes include: absolute decrease in urine albumin-to-creatinine ratio (ACR) after 6 months of treatment compared with baseline at randomization; the percentage of patients who have achieved complete response, defined as proteinuria less than 0.3 g/d and serum albumin ≥3.5 g/dL; the percentage of patients who have achieved partial response, defined as a decrease in proteinuria ≥50% compared with the level at randomization.

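### The plan tests the primary outcome with an unadjusted test and again with ANCOVA, both at P < .05, and does not say which result decides

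*Protocol article*

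**What the plan says.** Section 2.7.1 (Efficacy outcomes) defines a change score: "Primary efficacy outcome is absolute decrease in proteinuria after 6 months of treatment compared with baseline at randomization".

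Section 2.11 (Data analysis) covers all continuous variables in one sentence: "Student *t* test or Wilcoxon rank sum test for continuous variables will be applied to detect the differences between the intervention and the control groups". It then adds a baseline-adjusted model: "analysis of covariance will be conducted using proteinuria at baseline as a covariant to further evaluate the difference between these 2 groups". One threshold follows for everything: "A 2-tailed *P* < .05 will be considered to be significant".

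Section 2.10 (Sample size) gives the error rate and allocation, "the sample size calculated with type I error of 0.05 (bilateral) and a randomization ratio of 1:1", and the target, "to provide a power of 80% to detect an effect size of 2 g/d is 9 per group". It names no test. The only SD in the article is in the same section: "The average amount of proteinuria in this population was 2.89 ± 0.62 g/d at the time of diagnosis".

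Section 2.11 does not mention the primary outcome by name. Applying its tests to that outcome is an inference, but it is the only natural one, because proteinuria is the covariate in the model.

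**The concern.** Two analyses answer the same question about the same outcome at the same threshold. If one is significant and the other is not, the plan does not say whether the trial has succeeded. The trial is open-label and small, so the deciding analysis should be settled before the data are seen. Otherwise the false-positive rate of the primary claim exceeds the stated 5%.

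The order also matters. The unadjusted comparison comes first and ANCOVA is described as a further look. With simple randomization of 20 patients, chance differences in baseline proteinuria can be sizeable, and an unadjusted change score carries part of such a difference into the estimate.

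**Working it through.** **Inputs.** From the article: two-sided alpha 0.05, 1:1 allocation, 9 evaluable per arm (10 enrolled), planned difference 2 g/d, SD 0.62 g/d at diagnosis. Assumed: normal data, equal SD at baseline and month 6, and a baseline to month-6 correlation r of 0.3 to 0.7, with 0.9 as a boundary check.

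**1. The plan's own figure.** With difference 2 and SD 0.62, the exact t calculation needs 3 per arm (power 83% at 3, 43% at 2), not 9. The stated 9 corresponds to an unstated SD of about 1.35 to 1.42 g/d. This is a separate matter, but it bears on step 4.

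**2. False-positive chance under no effect.** Simulation with 40,000 trials per setting (Monte Carlo error about 0.1 percentage point). The entries give the chance of P < .05 for ANCOVA alone, and of at least one P < .05 for the combinations:

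| Per arm | r | ANCOVA alone | t and ANCOVA | Wilcoxon and ANCOVA | Any of three |
|---|---|---|---|---|---|
| 9 | 0.3 | 5.0% | 7.8% | 7.0% | 8.2% |
| 9 | 0.5 | 4.8% | 7.2% | 6.6% | 7.6% |
| 9 | 0.7 | 4.9% | 6.7% | 6.4% | 7.2% |
| 10 | 0.3 | 4.9% | 7.7% | 7.3% | 8.2% |
| 10 | 0.5 | 4.9% | 7.2% | 6.9% | 7.7% |
| 10 | 0.7 | 5.2% | 7.1% | 6.9% | 7.6% |

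The literal reading is one of the two middle columns. The t and ANCOVA results disagree on significance in 2 × P(either) − P(t) − P(ANCOVA) of null trials. At 9 per arm and r = 0.3 this is 2 × 0.0778 − 0.0515 − 0.0496 = 5.5%. At r = 0.7 it is 2 × 0.0674 − 0.0490 − 0.0490 = 3.7%.

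**3. Precision.** In large samples the ratio of ANCOVA variance to change-score variance is (1 − r²) / (2(1 − r)) = (1 + r)/2. Estimating the slope from n per arm multiplies this by 1 + 1/(2n − 4), which is 1.071 at n = 9 and 1.063 at n = 10.

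- r = 0.3: 0.65 × 1.063 to 0.65 × 1.071 = 0.69 to 0.70
- r = 0.7: 0.85 × 1.063 to 0.85 × 1.071 = 0.90 to 0.91
- r = 0.9: 0.95 × 1.063 to 0.95 × 1.071 = 1.01 to 1.02, so no gain

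**4. Power.** The change SD is 0.62 × √(2(1 − r)), that is 0.73, 0.62 and 0.48 g/d at r = 0.3, 0.5 and 0.7.

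- At the planned 2 g/d, both tests have at least 99.9% power.
- At an illustrative 0.6 g/d (an assumption, not in the article) and 10 per arm, t against ANCOVA is 41% v 55%, 54% v 63% and 75% v 79%. The two disagree on significance in about 24%, 19% and 11% of trials.
- If the change SD were about 1.42 g/d, so that the t test has 80% power for 2 g/d at 9 per arm, ANCOVA would have about 92%, 88% and 83%.

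**5. Baseline imbalance.** If the SD at diagnosis also held at randomization (an assumption, since patients enter after at least 3 months of ACEi/ARB), the SE of the chance baseline difference at 10 per arm is 0.62 × √(2/10) = 0.28 g/d. An imbalance of that size shifts the unadjusted change difference by (1 − r) × 0.28 = 0.19, 0.14 or 0.08 g/d.

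**The case against.** A reader might infer that three P values will be reported. The text does not support that: t and Wilcoxon are offered as alternatives, so two are reported, and the any-of-three column above is an upper bound. A rule for choosing between t and Wilcoxon is commonly left to an analysis plan, and its absence is not held against the article.

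A reader might also infer that putting the unadjusted test first leaves the trial short of power. On the article's own figures it does not, because either test detects 2 g/d almost with certainty at SD 0.62. ANCOVA's advantage also depends on a correlation that the article does not give.

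It is tempting to call the reason given for ANCOVA, possible spontaneous remission, an error. The control arm does deal with remission unrelated to treatment. But if remission depends on baseline proteinuria, adjusting for baseline is a reasonable response. The wording is terse rather than shown to be wrong, and it changes no result.

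Two further points stand. The change score is unbiased over repeated randomizations, so the shift in step 5 applies only given an observed imbalance, and the planned ANCOVA would correct it. Also, all the simulations assume normal data, whereas the article allows for skewed data.

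None of this answers the central point. The published text itself sets two tests on one difference at one threshold and ranks neither.

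**Conclusion.** The point holds as a matter of ranking, not of a missing method. The primary claim can rest on either of two P values. Under the stated assumptions (normal data, 9 to 10 per arm, r of 0.3 to 0.7), the chance of at least one false-positive result is about 7 to 8% with t and ANCOVA, and slightly lower (6.4 to 7.3%) if Wilcoxon takes the place of t. ANCOVA alone holds about 5%. The inflation is moderate because the tests are strongly correlated.

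ANCOVA is the better choice to decide for correlations up to roughly 0.8, and about equal to the t test near 0.9. The power gain has practical weight only if the true effect is well below 2 g/d or the SD well above 0.62 g/d. The 0.6 g/d power figures and the 0.28 g/d baseline SE are illustrations that rest on assumptions. This should be changed before analysis, but it does not invalidate the design.

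**What to change.** State in section 2.11 that the single primary analysis is ANCOVA of month-6 proteinuria (or its change) on treatment group and baseline proteinuria, reporting the adjusted difference, its 95% confidence interval and the two-sided P value, and that this P value alone decides the primary claim. Label the t and Wilcoxon tests supportive, with Wilcoxon as the sensitivity check for non-normal data. Use the same model with baseline ACR as covariate for the ACR outcome.

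The change takes about two sentences and needs no new data, since urine tests are scheduled at randomization and at day 180. The cost is one degree of freedom and reliance on a linear model in a sample of about 18 to 20 patients, which is why the rank test should be kept as a check.
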